### Follow-up procedure

2.11

Participants allocated to the adjuvant TACE group will receive a single TACE procedure following hepatic angiography, followed by standardized intensive follow-up, whereas those in the intensive follow-up group will undergo surveillance alone after angiography. Follow-up assessments will be conducted every 3 months (±7 days) from the time of first intervention, and every 6 months (±7 days) after 2 years. At each visit, participants will undergo comprehensive evaluation, including contrast-enhanced CT or MRI of the chest and upper abdomen, measurement of tumor markers such as alpha-fetoprotein and abnormal prothrombin, and additional assessments as detailed in Table 1.

**Table 1 tbl1:** Schedule of study assessments and study timeline.

Phase	Screening period	TACE treatment period	Safety Visit o	Survival Visit p
		C1/D1		
Days	−28∼-1	1	30 days Post-TACE	Every 90 days
Time Window (Days)	NA	+3	±7	±7
**General Study Process**				
Written Informed Consent^a^	×			
Inclusion/Exclusion Criteria	×			
Demographics/Medical History/Prior Treatment History b	×			
Previous Concomitant Medications	×	×	×	
Vital Signs^c^	×	×	×	
Weight/Height^d^	×	×	×	
Comprehensive Physical Examination	×	×	×	
Eastern Cooperative Oncology Group performance status	×	×	×	
12-lead Electrocardiogram (ECG) e	×	×		
**Laboratory Assessment**				
Complete Blood Count f	×	×	×	
Blood Biochemistry f	×	×	×	
Urinalysis f	×	×	×	
Coagulation Profile g	×	×	×	
Pregnancy Test h	×			
Thyroid Function Tests i	×	×	×	
Cardiac Enzyme Panel i	×	×	×	
Virological Antibody Testing j	×			
If HCV antibody is positive, test for HCV RNA k	×			
If HBsAg and/or HBcAb are positive, test for HBV-DNA l	×	×	×	
**Safety Monitoring and Survival**				
Adverse Event Assessment m	×	×	×	×
Subsequent Anti-tumor Treatment				×
Survival Status				×
**Efficacy Assessment**				
Tumor Imaging Assessment n	×		×	
**Investigational Drug Administration**				
TACE		×		

Notes.

a Written informed consent must be obtained prior to initiation of any protocol-specified procedures.

b Prior antitumor treatment history includes all therapies administered for HCC, such as chemotherapy, radiotherapy, and surgical interventions.

c Vital signs include body temperature, pulse rate, respiratory rate, and blood pressure.

d Height will be measured only during the Screening Period. Body weight will be recorded prior to each treatment administration. If body weight varies by less than 10% from baseline (defined as the day of first study treatment), baseline weight will be used for dose calculations; otherwise, the weight measured on the day of treatment will be used.

e A 12-lead ECG will be performed during the Screening Period, prior to each treatment cycle beginning from Cycle 2, and during the safety follow-up period.

f Complete blood count includes red blood cell count, hematocrit, hemoglobin, platelet count, white blood cell count, and differential counts (lymphocytes, monocytes, neutrophils, eosinophils, and basophils). Blood biochemistry includes liver function parameters (total bilirubin, direct bilirubin, aspartate aminotransferase, alanine aminotransferase, γ-glutamyl transferase, albumin, total protein, alkaline phosphatase, lactate dehydrogenase, and creatine kinase), renal function markers (urea and creatinine), blood electrolytes (sodium, potassium, chloride, magnesium, calcium, phosphorus), amylase, and blood glucose. Urinalysis includes pH, urine protein, red blood cells, white blood cells, glucose, and specific gravity. Participants with urine protein ≥2+ at screening will undergo 24-h urine protein quantification. These assessments will be performed within 7 days prior to first treatment, prior to each subsequent cycle (from Cycle 2 onward), and during safety follow-up. All tests will be conducted at study sites.

g Coagulation profile includes prothrombin time and international normalized ratio. Assessments will be performed within 7 days prior to first treatment, prior to subsequent treatment cycles (from Cycle 2 onward), and during safety follow-up at each study site.

h Female participants of childbearing potential will undergo serum pregnancy testing within 72 hours prior to the first treatment administration. If urine testing is inconclusive, serum testing will be used for confirmation. All tests will be conducted at study sites.

i Thyroid function tests and cardiac enzyme panels will be performed within 28 days prior to first treatment, prior to each treatment cycle (from Cycle 2 onward), and during safety follow-up at study sites.

j Virological testing includes human immunodeficiency virus, HCV antibody, and hepatitis B panel (HBsAg, HBsAb, HBcAb, HBeAg, HBeAb), performed within 28 days prior to first treatment during screening.

k For participants with positive HCV antibody, HCV-RNA viral load will be assessed every (21 ± 7) days from first treatment or earlier if clinically indicated.

l For participants with positive HBsAg and/or HBcAb, HBV-DNA viral load will be assessed every (21 ± 7) days from first treatment or earlier if clinically indicated.

m Adverse events and laboratory safety parameters will be evaluated according to Common Terminology Criteria for Adverse Events version 5.0. Definitions, grading, causality assessment, reporting timelines, and management procedures are specified in Section 8 of the protocol.

n Tumor assessments will be conducted in accordance with Response Evaluation Criteria in Solid Tumors version 1.1 (RECIST 1.1)^36^ and modified RECIST (mRECIST).^37^ Imaging evaluations will primarily consist of contrast-enhanced computed tomography (CT) or magnetic resonance imaging (MRI), with mandatory inclusion of thoracic and abdominal regions. At baseline, within 28 days prior to enrollment, additional imaging assessments—including pelvic CT or MRI, cranial MRI, and whole-body bone scan—are required. If cervical lymph node enlargement is present, contrast-enhanced neck CT should also be performed. Positron emission tomography/computed tomography (PET/CT) may be used as a baseline screening modality; if abnormalities are detected, corresponding contrast-enhanced CT or MRI examinations must be performed to facilitate subsequent longitudinal comparisons. For participants without evidence of metastatic disease at baseline, routine cranial, pelvic, and whole-body bone imaging is not required during follow-up unless clinically indicated. Imaging modalities and techniques should remain consistent throughout the study for each participant. Tumor imaging evaluations will be performed every 6 weeks (±7 days) starting from the first administration of investigational treatment, and subsequently every 12 weeks (±7 days) after 54 weeks. Upon the first radiological assessment indicating progressive disease based on RECIST 1.1, participants with clinically stable disease, absence of rapid radiological progression, and investigator-determined potential for continued clinical benefit may continue the current investigational treatment. In such cases, a confirmatory imaging assessment must be performed after a minimum interval of 4 weeks in accordance with RECIST 1.1. If progression is confirmed, the participant must discontinue investigational treatment; if not confirmed, treatment may continue with ongoing imaging evaluations per the protocol-defined schedule until radiologically confirmed progression. For participants who discontinue investigational treatment for reasons other than objective disease progression, tumor imaging assessments must be conducted at the time of treatment discontinuation and continued thereafter according to the protocol-specified schedule until the earliest occurrence of initiation of new antitumor therapy, confirmed disease progression, loss to follow-up, death, or withdrawal of informed consent. Unscheduled imaging assessments may be performed at any time if clinically indicated. In cases of clinically unstable disease following initial radiological progression, confirmatory imaging after 4–6 weeks is not required, and investigational treatment should be discontinued immediately.

o Safety follow-up will be conducted at (30 ± 7) days after TACE treatment or prior to the initiation of any new antitumor therapy, whichever occurs first. All adverse events (AEs) that occur prior to the safety follow-up visit must be documented and followed until resolution to Grade 0–1 return to baseline status, or until the investigator determines that further follow-up is not clinically warranted based on appropriate justification (e.g., no reasonable expectation of recovery or clear clinical improvement), whichever occurs first. Serious adverse events (SAEs) occurring within 90 days after study treatment administration or prior to the initiation of subsequent antitumor therapy (whichever occurs first) must be continuously monitored and documented in detail until resolution, stabilization, or return to baseline clinical status, in accordance with protocol-defined safety reporting procedures.

p Survival follow-up will be conducted every 90 days (±7 days) after completion of the safety follow-up visit. These follow-up assessments may be performed via in-person visits or telephone contact, as appropriate, to collect survival status and relevant clinical information.

The participant timeline is illustrated in Fig. 1.

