### Patients

2.6

Following hepatic angiography confirming the absence of intrahepatic tumor staining, eligible participants will be randomly assigned in a 1:1 ratio to either the adjuvant TACE group or the intensive follow-up group. In the adjuvant TACE group, participants will undergo a single session of TACE after confirmation of no tumor staining on hepatic arteriography, followed by standardized intensive follow-up. Participants allocated to the intensive follow-up group will receive routine surveillance only after hepatic angiography. Patients in both groups were followed until death or study termination. Key landmarks defining follow-up cessation included: disease progression (defined as HCC recurrence or metastasis), death, withdrawal of informed consent, initiation of a new antitumor therapy, or any other protocol-specified reason for treatment discontinuation.

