### Interventions

2.8

All enrolled participants will undergo hepatic arteriography 4–8 weeks following curative hepatectomy. With the patient in the supine position, standard aseptic preparation and sterile draping of the right groin will be performed. After local anesthesia with 5 mL of 2% lidocaine at the right femoral artery puncture site, a 5F arterial sheath will be inserted using the Seldinger technique. A 5F hepatic catheter will then be advanced into the celiac trunk for angiographic assessment. The hepatic arterial system, including the left and right hepatic artery branches, will be systematically evaluated to identify intrahepatic tumor staining. Detection of one or more foci of tumor staining will indicate that the initial hepatectomy did not meet criteria for curative resection, and such patients will be excluded. Participants without evidence of tumor staining will be randomly assigned to either the adjuvant TACE group or the intensive follow-up group.

In the adjuvant TACE group, superselective catheterization will be performed targeting the hepatic resection margin, followed by embolization using an emulsion of 50 mg lobaplatin and 3–5 mL ethiodized poppyseed oil. This regimen is based on prior RCTs demonstrating a reduction in postoperative HCC recurrence with adjuvant TACE.^30^^,^^31^ Polyvinyl alcohol embolic microspheres will not be utilized, as they are not part of the standard adjuvant protocol. In the intensive follow-up group, hepatic arteriography will be performed without administration of embolic or chemotherapeutic agents. Upon completion of the procedure, the catheter and arterial sheath will be removed, and manual compression will be applied to achieve hemostasis. Adjuvant TACE will be administered as a single session only.

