#### Sequence generation

2.9.1

Randomization will be performed using computer-generated random number tables managed by Good Clinical Practice-compliant research centers at participating sites. Personnel responsible for sequence generation will have no involvement in study conduct. The interval between randomization and administration of adjuvant TACE will not exceed 1 week. During angiography, if tumor staining is identified in the remnant liver, TACE will be performed for clinical management; however, such participants will be excluded from the study.

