#### Blinding

2.9.4

This study adopts a multiple blinding design. The doctor performing interventional operations will be aware of treatment allocation, whereas investigators, participants and data analysts will remain blinded throughout the study until unblinding.

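### Table 1 dates the 30-day safety visit from TACE, which the intensive follow-up group does not receive, so as written only one arm has a scheduled early safety check

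*Protocol article*

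**What the plan says.** Table 1 is a single schedule for the whole trial. Its safety-visit column is headed "30 days Post-TACE", and note o places the visit at 30 ± 7 "days after TACE treatment or prior to the initiation of any new antitumor therapy, whichever occurs first". Note o also sets a follow-up window for serious adverse events "occurring within 90 days after study treatment administration". Note p counts the 90-day survival visits from completion of the safety visit.

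Section 2.8 describes the comparator: "In the intensive follow-up group, hepatic arteriography will be performed without administration of embolic or chemotherapeutic agents". Section 2.6 states the order of events: "Following hepatic angiography confirming the absence of intrahepatic tumor staining, eligible participants will be randomly assigned". Section 2.9.1 adds: "The interval between randomization and administration of adjuvant TACE will not exceed 1 week".

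Section 2.11 gives both groups visits every 3 months "from the time of first intervention, and every 6 months" after 2 years, with a broad evaluation that refers back to Table 1 for further assessments. Section 2.9.4 says that the interventional operator knows the allocation, "whereas investigators, participants and data analysts will remain blinded throughout the study until unblinding".

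**The concern.** A visit dated from TACE has no date in an arm that never receives TACE. Safety and tolerability is a key secondary endpoint, and section 2.1 defines its adverse events without regard to causality. What is counted therefore depends on when and how closely each arm is examined. If one arm has a planned examination and laboratory panel a month after the procedure and the other does not, short-lived events such as transient laboratory changes may be found in one arm and missed in the other. A visit held only in the TACE arm would also tell participants and site staff who had been treated.

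**Working it through.** No figure in the plan can be reproduced here, because the point is about an anchor date. The check sets the sections side by side and does simple date arithmetic.

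**1. Is there another 30-day anchor for the follow-up group?** Heading and note o both name TACE. Section 2.8 gives this group arteriography alone, and section 2.6 gives it surveillance only after that. The second limb of note o, before any new antitumor therapy, dates a visit only for a participant who starts such therapy. No other section supplies a date.

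**2. What depends on the anchor?** The 90-day window in note o runs from study treatment. The survival visits in note p run from the safety visit. Notes f to l count from first treatment, and note n from first administration of investigational treatment. Section 2.11 uses first intervention, a term that can cover angiography, but it does so for a different series of visits.

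**3. What does the visit contain?** Rows ticked in Table 1 at the safety visit: 5 general, 7 laboratory, 1 adverse event and 1 imaging, so 5 + 7 + 1 + 1 = 14. Adverse event assessment is ticked again at survival visits, and HBV-DNA and imaging recur through notes l and n. That leaves 14 − 3 = 11 rows, including physical examination, blood count and biochemistry, with no later tick or repeat date in Table 1 and its notes for this single-session trial.

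**4. When is each group first seen?**
- TACE group, note o: 30 ± 7 = day 23 to 37.
- Both groups, section 2.11: 91 ± 7 = day 84 to 98.
- Note l, HBV-DNA in participants positive for HBsAg or HBcAb: 21 ± 7 = day 14 to 28.
- Note n, imaging: 42 ± 7 = day 35 to 49.

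The last two are counted from treatment, so whether they apply to the follow-up group is itself unclear. If they do, that group has contacts well before month 3, but for a viral load or a scan and not for the full panel. If they do not, its first dated contact is at month 3, that is 91 − 30 = 61 days later (84 − 37 = 47 to 98 − 23 = 75).

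**5. How many participants?** 442 / 2 = 221.

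**6. Recurrence-free survival.** The safety visit includes imaging, so one arm could have one extra scan. Simulation with no true effect, hazard ln(2)/16.1 per month, 24 to 36 months of follow-up and 1,500 runs per setting gave these results with against without a day-30 scan in the TACE arm only:
- 3-monthly imaging: mean hazard ratio 1.014 against 1.007 (simulation standard error 0.003), two-sided 5% rejection 4.4% against 4.8%.
- 6-weekly imaging: mean hazard ratio 1.008 in both, rejection 5.9% against 5.5%.

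The extra scan makes no practical difference.

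**The case against.** The strongest reply is that this is a loose label. The day-1 column is also headed with TACE, and read just as literally the follow-up group would have no day-1 assessments at all. The notes carry wording about later cycles that does not fit a single-session trial, which suggests a reused template. Section 2.16 counts safety reviews by participants who have had DSA, in both arms, so the visit may well have been intended for both. The notes also point to safety procedures in a fuller protocol that is not shown. All of this bears on intent and is fair. It does not change the fact that the article prints a complete schedule with an explicit anchor, and that the anchor does not exist for half the trial.

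The reply also rightly limits the consequences, and three stronger readings should be resisted:
- *The follow-up group has no safety follow-up.* It has the 3-monthly visits of section 2.11 with their reference back to Table 1, and section 2.17.2 requires all adverse events to be documented. Because section 2.11 dates visits without using note p, the survival series is not lost in practice.
- *There is a 61-day gap in all contact.* That holds only if notes l and n do not apply to this group.
- *The adverse event comparison will show a false difference.* With 221 per arm, assuming that 5% have an event a day-30 visit would find, 11 against 0 gives Fisher p = 0.0009, but only if none is captured later. Capturing about half gives 11 against 6, p = 0.32, and capturing all gives no difference. The rate and the capture fractions are assumptions, and the article names no between-arm test of adverse events.

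The blinding point is conditional too. If TACE is given in the angiography session and both groups attend, the visit date reveals nothing.

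**Conclusion.** The point holds as a defect of wording with a possible practical effect. As written, a scheduled 30-day examination and laboratory check exists only in the TACE group, and the 90-day serious adverse event window has the same gap. Detection of early or transient adverse events could then differ between arms, and a TACE-only visit would conflict with the stated blinding. The size of the effect on adverse event counts cannot be derived from the document: it runs from none, if sites apply the visit to both groups or later contacts capture everything, upwards by an unknown amount. Recurrence-free survival is practically unaffected. This is a minor point, worth correcting because the correction is cheap. It rests on the article alone; the fuller protocol may already state a common anchor.

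**What to change.** Head the column *30 days after the day-1 procedure (both groups)*. In note o, date both the safety visit and the 90-day serious adverse event window from the day-1 procedure, meaning angiography with TACE or angiography alone, in both groups. Use the same anchor where notes f to l and n refer to first treatment or first administration of investigational treatment. Note p then needs no change.

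If TACE can be given in a later session than the angiography, as the one-week allowance in section 2.9.1 might permit, use randomization as the common anchor in both groups. With the intervals unchanged and TACE 0 to 7 days after randomization, the visit would fall 23 − 7 = 16 to 37 days after TACE, and the window would end 90 − 7 = 83 to 90 days after it.

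Cost: text edits only, if the visit was meant for both groups. Otherwise about 221 additional day-30 visits in the follow-up group.

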### Sample size calculation

2.12

Sample size estimation was performed using PASS 2021 (version 21.0.3) for a noninferiority randomized controlled trial. Based on historical data from our center, the median RFS for patients with high-risk recurrence factors managed with intensive follow-up alone was 16.1 months,^13^ corresponding to a hazard rate of 0.043 (ln(2)/16.1). Enrollment is planned over 1 year, followed by at least 2 years of follow-up. With a one-sided α of 0.025, 80% power, and a 1:1 allocation ratio, 192 participants per group (total *n* = 384) are required to demonstrate noninferiority at a hazard ratio margin of 1.4, with an estimated 139 events per group. Assuming an annual attrition rate of 5%, an additional 58 participants are required, yielding a total sample size of 442.

Sensitivity analysis was conducted using an alternative median RFS of 19.0 months derived from a cohort excluding DSA-positive patients,^34^ corresponding to a hazard rate of 0.0365 (ln(2)/19.0). Under similar assumptions, 360 and 361 participants would be required in the experimental and control groups, respectively (total *n* = 721), to achieve 80% power at the same noninferiority margin. Given the practical constraints of an investigator-initiated study without commercial funding, enrollment of more than 700 participants is not feasible; therefore, a target sample size of at least 442 participants has been selected to ensure study reliability.

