### Objectives

2.1

This study is a multicenter phase III RCT, aims to rigorously evaluate the clinical efficacy of adjuvant TACE of HCC patients with high-risk recurrence factors following curative hepatectomy. The primary endpoint of this study is to investigate whether adjuvant TACE could improve RFS in high-risk HCC patients following curative hepatectomy. The key secondary endpoints include the safety and tolerability of adjuvant TACE—such as incidence of treatment-related adverse events (TRAEs) and serious adverse events (SAEs), and the rate of treatment discontinuation attributable to TRAEs or SAEs—as well as the effects of adjuvant TACE versus intensive follow-up on OS, median RFS, and time to tumor recurrence.

RFS is defined as the interval from randomization to the first imaging-confirmed recurrence of HCC—whether intrahepatic or extrahepatic—or death from any cause. TRAEs is defined as any unfavorable or unintended medical occurrences following informed consent, irrespective of causality. SAEs is defined as events that result in death, are life-threatening, require hospitalization or prolong hospitalization, result in persistent or significant disability, cause congenital anomalies, or represent other medically significant conditions. OS is defined as the time from randomization to death from any cause; time to recurrence, defined as the interval from curative hepatectomy to first imaging-confirmed recurrence.

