### Statistical methods

2.13

All statistical analyses will be performed using SAS software (version 9.2). A one-sided superiority testing framework will be applied, with a significance level (α) of 0.05. Between-group comparisons will be reported with corresponding *p*-values and 95% confidence intervals. Continuous variables will be summarized as mean ± standard deviation for approximately normally distributed data, or as medians otherwise. Categorical variables will be presented as frequencies and percentages. Survival outcomes, including median RFS and OS, will be estimated using the Kaplan–Meier method with corresponding 95% confidence intervals. Group comparisons will be performed using the log-rank test, and survival curves will be generated accordingly.

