## Discussion

3

Hepatic resection and local ablation remain the primary curative treatment modalities for HCC; however, long-term outcomes are substantially limited by high recurrence rates, with approximately 70% of patients experiencing recurrence within 5 years after resection.^2^^,^^3^ The role of adjuvant therapy in this setting remains highly controversial. Notably, the IMbrave050 trial reported limited benefit of adjuvant immune checkpoint inhibition, leading most international guidelines to recommend intensive follow-up rather than routine postoperative therapy.^20^ By contrast, the CNLC strongly endorses TACE as an adjuvant strategy following curative hepatectomy,^17^^,^^29^ primarily based on two RCTs published in 2018.^30^^,^^31^ However, critical methodological limitations are evident in these studies, particularly the absence of explicit exclusion of patients with tumor staining identified on hepatic arteriography, which may reflect residual intrahepatic disease and thus incomplete, non-curative resection. A more recent RCT in patients with American Joint Committee on Cancer TNM stage I/II HCC demonstrated that adjuvant TACE does not improve RFS in those who have undergone true curative resection.^33^ These observations support the hypothesis that the apparent benefit of adjuvant TACE reported in earlier studies may be attributable to the treatment of residual lesions following non-radical resection, rather than to the intrinsic pharmacologic or embolic effects of TACE. Accordingly, when curative standards are achieved, defined by the absence of tumor staining on DSA, adjuvant TACE may confer no additional therapeutic advantage.

To address these unresolved issues, the present study was designed as a rigorously conducted multicenter phase III RCT that prioritizes confirmation of curative resection and excludes patients with tumor staining. This trial evaluates the impact of adjuvant TACE on RFS in patients with HCC who have high-risk recurrence factors following curative hepatectomy. A total of 442 participants will be enrolled, exceeding the sample sizes of prior studies^30^^,^^31^^,^^33^ to generate more robust and definitive evidence regarding the potential survival benefit of adjuvant TACE in this population. Overall, this trial is intended to provide high-level evidence to inform precision management strategies for HCC, support refinement of clinical guidelines, and promote the efficient allocation of healthcare resources.

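### The trial is sized for noninferiority at one-sided 0.025 but analysed for superiority at one-sided 0.05, so the stated 80% power is not that of the planned test

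*Protocol article*

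**What the plan says.** Section 2.12 (Sample size calculation) presents the design as noninferiority: "Sample size estimation was performed using PASS 2021 (version 21.0.3) for a noninferiority randomized controlled trial". The settings are "With a one-sided α of 0.025, 80% power, and a 1:1 allocation ratio", and the resulting numbers "are required to demonstrate noninferiority at a hazard ratio margin of 1.4, with an estimated 139 events per group". That gives 192 patients per group, 384 in total, raised to 442 for attrition. The sensitivity calculation in the same section keeps the same margin.

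Section 2.1 (Objectives), like the Abstract, sets a superiority question: "The primary endpoint of this study is to investigate whether adjuvant TACE could improve RFS in high-risk HCC patients following curative hepatectomy".

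Section 2.13 (Statistical methods) also plans superiority, at a different alpha: "A one-sided superiority testing framework will be applied, with a significance level (α) of 0.05". Groups are compared by log-rank test, and between-group comparisons carry p-values and 95% confidence intervals. The margin of 1.4 does not appear there.

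The Discussion expects that, once patients with tumor staining are excluded, "adjuvant TACE may confer no additional therapeutic advantage".

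**The concern.** The sections disagree on two things that fix what the trial can claim: the hypothesis (exclude a hazard ratio of 1.4, or show a hazard ratio below 1) and the one-sided alpha (0.025 or 0.05). This is a conflict between two stated passages, so an analysis plan that is not shown could not make both true.

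Three further gaps follow from it:

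- No superiority effect size is given, so no power is stated for the test in 2.13.
- The arm to be shown noninferior is not named. Section 2.12 takes its reference rate from intensive follow-up and speaks of experimental and control groups, which suggests TACE is to be shown noninferior to follow-up. The Discussion points the other way, towards follow-up being good enough without TACE.
- No rule says how a confidence limit is to be compared with 1.4.

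At stake is the primary conclusion. The same data could be reported as TACE not superior, TACE noninferior to follow-up, or follow-up noninferior to TACE, with the choice made after the results are known. Section 2.16 also plans an interim RFS analysis with sample size reassessment, and a reassessment needs a defined target test.

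**Working it through.** **Inputs, all from section 2.12 unless noted.** Margin 1.4; one-sided alpha 0.025; power 80%; allocation 1:1. Control rate: "the median RFS for patients with high-risk recurrence factors managed with intensive follow-up alone was 16.1 months". Timeline: "Enrollment is planned over 1 year, followed by at least 2 years of follow-up". From section 2.13: one-sided alpha 0.05 for the superiority test. My assumptions: exponential RFS, uniform accrual over 12 months, exactly 24 months of follow-up after accrual closes, and a true hazard ratio of 1 for the sizing (2.12 does not state it).

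**1. Reproduce the plan's figure.**

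- Events (Schoenfeld) = 4(1.960 + 0.8416)² / (ln 1.4)² = 277.3, rounded up to 278, or 139 per group. This matches.
- Monthly hazard λ = ln 2 / 16.1 = 0.04305.
- P(event) = 1 − [exp(−24λ) − exp(−36λ)] / (12λ) = 1 − (0.3558 − 0.2123) / 0.5166 = 0.722.
- N = 277.3 / 0.722 = 384. This matches.
- 384 × 1.15 = 441.6, rounded up to 442. This matches.

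The arithmetic is therefore noninferiority arithmetic throughout, and its 80% holds at a true hazard ratio of 1.

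**2. Power of the test in 2.13.** Power = Φ(½√D × |ln HR| − z), with z = 1.645 at one-sided 0.05 or 1.960 at 0.025. HR is TACE vs follow-up, and D is the number of events. The HRs below 1 are an assumed range, because the protocol gives none.

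| True HR | Events, 384 patients on the stated timeline | Power, 0.05 | Power, 0.025 |
|---|---|---|---|
| 1.00 | 277 | 5% (type I error) | 2.5% (type I error) |
| 0.90 | 270 | 22% | 14% |
| 0.85 | 266 | 37% | 26% |
| 0.80 | 262 | 56% | 44% |
| 0.75 | 257 | 75% | 64% |
| 0.714 | 254 | 85% | 76% |

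Worked row, HR 0.80: the TACE event probability at hazard 0.8λ is 0.642, so D = 192 × (0.722 + 0.642) = 262. Then ½√262 × 0.2231 = 1.806. Φ(1.806 − 1.645) = 56% and Φ(1.806 − 1.960) = 44%.

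**3. Superiority effect detectable with 278 events at 80% power.** HR = exp[−2(z + 0.8416) / √278].

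- One-sided 0.025: 0.714, i.e. 1/1.4, a median of 16.1 / 0.7146 = 22.5 months.
- One-sided 0.05: 0.742, a median of 16.1 / 0.742 = 21.7 months.

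**4. Sensitivity to the attrition allowance.** Step 2 gives the 58 extra patients no events. If all 442 contribute until dropout at an exponential 5% per year, HR 0.80 gives about 286 events and power of 60% (0.05) or 47% (0.025). HR 0.714 gives about 277 events and 80% at 0.025. The mismatch in step 2 remains either way.

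**The case against.** The strongest reply is that the event count is not wasted on superiority. By symmetry on the log scale, 278 events give 80% power for superiority at HR 0.714 with one-sided 0.025. At the alpha in 2.13 they give 80% at about 0.742 and 88% at 0.714. This stands. A reader might infer that the sample size cannot serve any analysis in 2.13, and that goes too far. What is missing is a statement and justification of the effect for which 80% holds.

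A reader might also infer that, if TACE has no effect, the trial could conclude nothing. The documents do not support that either. Section 2.13 promises 95% confidence intervals. If these include one for the hazard ratio, an observed value of 1 with 278 events gives about exp(±1.96 × 2/√278), or 0.79 to 1.27, which excludes both 1.4 and 0.714. The superiority test would not reject, but the interval would be informative. The plan lacks a prespecified rule for drawing a conclusion from it. The 5% rejection rate at HR 1 is type I error and not a loss of power.

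Two limits on the point also stand. Direction is implied to some extent by the reference rate and arm labels in 2.12, so the fair statement is that it is not explicit. The lack of a named Cox model in a journal article is ordinary analysis-plan detail and no part of this finding.

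**Conclusion.** The point holds. Sections 2.12 and 2.13 contradict each other on hypothesis and on alpha, and 2.1 agrees with 2.13 on superiority. The stated 80% is noninferiority power at a true hazard ratio of 1 and one-sided 0.025. It is not the power of the planned test, which is 5% at HR 1 and about 56% at an assumed HR of 0.80 (44% at one-sided 0.025) with 384 patients. Those figures rest on exponential survival, uniform accrual, the 16.1-month median and the stated minimum follow-up. The HR of 0.80 is illustrative. The contradiction itself rests on no assumption. It must be corrected before the trial reports, because it decides which claim the primary result can support.

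**What to change.** State one hypothesis, one alpha and one hazard ratio orientation (TACE vs follow-up) in 2.1, 2.12 and 2.13, and use the same target in the interim reassessment in 2.16.

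**(a) If superiority is the aim, as 2.1 and 2.13 say.** Replace the noninferiority sizing with the effect that the planned events can detect: about 278 events, 80% power at HR 0.714 (one-sided 0.025) or about 0.742 (one-sided 0.05), with a reason for expecting that effect. Trigger the analysis by events. If TACE works, events come more slowly: 384 patients on the fixed timeline give about 254 events at HR 0.714, and power of about 76% at one-sided 0.025.

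**(b) If noninferiority is kept.** Name the arm to be shown noninferior and justify 1.4 for that direction. Change the alpha in 2.13 to one-sided 0.025. Write the rule into 2.13 using the two-sided 95% confidence interval for the hazard ratio: upper limit below 1.4 for TACE noninferior to follow-up, or lower limit above 1/1.4 = 0.714 for follow-up noninferior to TACE. Align the objective in 2.1 with the choice.

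The cost is rewording in the protocol and wherever the objective is repeated, with no extra patients. The sponsor must commit to a direction and, under (a), accept that the detectable effect is large. Under (a), event-driven timing may also lengthen follow-up.
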